### Data collection

#### Blinding (masking)

Blinded assessments of observer-rated POSAS and colour measurement are performed by scar management HCPs prior to ± laser treatment. The participants are instructed not to divulge their allocation to HCP to maintain blinding. This means that both the observer-rated POSAS and colour measurement are conducted by someone blinded to treatment allocation.

The patient-rated POSAS (primary outcome) and the relevant QoL questionnaires are completed by the participant. Although this assessment cannot be blinded, it was felt, as informed by the PPI group, that the participant’s perspective should be paramount in this trial. It is accepted that this may bias the patient-rated POSAS result in that they will make their rating knowing to which treatment arm they had been allocated. However, blinded clinician-rated secondary outcomes are included. In addition, the data collection, statistical analysis and initial interpretation of the primary and secondary outcome results will be blinded.

#### Harms

The most serious adverse event in the use of a laser is retinal burn, which may lead to permanent blindness. All laser clinics/sites are subject to government guidelines. The Health and Safety at Work Act 1974 and the Management of Health and Safety at Work Regulations 1999 require the employer and employee to undertake reasonable and practical health and safety measures. This serves to minimise this risk though designation of a “Laser Controlled area”, as defined by the Control of Artificial Optical Radiation at Work Regulations (AOR) 2010, performance of a risk assessment, publication of local rules and use of Personal Protective Equipment. There are no necessary regulatory approvals. All laser sites in the study have appropriate laser safety precautions in place, as determined by the local Laser Protection Advisors.

The adverse events from PDL treatment include, but are not limited to:

BlistersScabbingExcessive oedemaExcessive pigmentation changesExcessive PainWorsening of the scarOther

The scar might be fragile at this early stage but blistering is unlikely. Redness and/or oedema are to be expected and usually resolve within 7 – 10 days. Changes in pigmentation are often caused by the burn injury and the subsequent scarring; hypopigmentation is often inevitable in burn scarring. Hyperpigmentation resolves or can be treated at a later stage using Q-switched lasers. There have been few documented occurrences of worsening of the scar using PDL.

#### Data collection methods

##### Scar assessment

At each assessment, the participant acclimatises for at least 20 minutes to allow blood flow and skin temperature to equilibrate. The participant remains seated for the duration of assessment. Where the participant has multiple, non-contiguous scars at different anatomical locations, the “worst” scar, as identified by the participant, is assessed and included in the study. It would be prudent to be mindful to avoid areas where they may be a future need for surgery such as areas where contractures are beginning to form.

Whichever treatment group the patient is assigned to, each time they return for assessment, **the same area of hypertrophic scarring must be assessed and treated.** This will be known as the ‘Study Scar’. The ‘Study Scar’ is the scar that the patient, and the designated research team member at weeks 0 and 26, must assess and consider for all their visits. It is important that the participant is aware of this.

The ‘Study Scar’ and each ROI must be selected at the enrolment appointment. Firstly, the scar to be treated and assessed must be identified as a whole; this will be known as the ‘Study Scar’. This will be chosen in agreement with the participant. Where the participant has multiple, non-contiguous scars at different anatomical locations, the ‘Study Scar’ is agreed and included in the study. It would be prudent to be mindful to avoid any area for the ‘Study Scar’ where they may be a future need for surgery such as areas where contractures are beginning to form. The ‘Study Scar’ can be up to about 200 cm^
2
^ in size. This limit has been determined as the conventional total area of burn scar that would normally be treated by laser in one visit. Regardless of study group, the limit or guidance for size of ‘Study Scar’ area is the same.

Only part of this hypertrophic scar must then be selected as the ‘Scar ROI’. This should be the part of the burn scar that is the **
*most problematic to the participant.*
** This is typically excessively red, thickened and firm to touch compared to normal, unburnt skin. An area 4 cm x 4 cm is the optimal size for selection. This will the scar region of interest or ‘Scar ROI’ and this is the area that will be used for the **ColorMeter measurements only**.

The ‘Comparison ROI’ is then identified. It should be an unburnt area of skin. This should be contralateral i.e. the corresponding area on the opposite side of the body. If that contralateral area is burnt also, then the most proximal area to the ‘Scar ROI’ should be identified. This is then drawn onto the ‘Comparison ROI’ map. Again, an (matching) area 4 cm x 4 cm is the optimal size.

Photographs are taken at initial assessment to identify the location of the scar and the assessment point. The investigator must be able to precisely relocate the previously measured site as this could be a source of error that could contribute the variability in scar measurements over time. Skin markers, where seen, are included in the image. A measurement sticker is positioned adjacent to the scar for scaling, and a colour wheel is placed in the frame for white balance. Both are integral to each photograph of the neighbouring scar. Photographs are repeated at each assessment.

POSAS is performed as detailed on the website (www.posas. org). The observer-rated POSAS is conducted by an HCP. The participant is asked to complete the patient POSAS.

Scar colour is measured using the colorimeter (DSM III, Cortex, Denmark). After calibration, measurements are performed 3 times on the area to be treated and 3 times on a representative adjacent, or symmetrically opposite area of normal skin and then averaged. The colorimeter is connected to a PC. The mean and standard deviation values of Erythema and Melanin are calculated in a spreadsheet (Excel) and these data are then transcribed to the Case Report Form.

The entire assessment takes 20 - 30 minutes. All data is sent to an encrypted folder on a password-protected Health and Social Care Network (HSCN - N3 networked) computer.

## QoL and economic evaluation

The participant will then complete the CARe scale, SF-12 survey and healthcare resource use questionnaires. The CARe scale questionnaire and SF-12 health-related QoL outcome measure are administered at baseline and at 6 months^
70
^ and have been chosen due to its potential to capture the mental health impacts of burns scarring. Secondary care resource use is collected from routine clinic data. Wider costs, such as primary and social care resource use, are collected using direct patient self-reports. Patient-incurred costs are also collected at baseline and follow-up, as part of the qualitative interviews.

## Qualitative interviews

A sample of participants (n=20, 10 in each arm) receive a telephone interview conducted by a qualitative researcher at approximately 26 weeks. An approximately equivalent proportion is selected from each burn location classification variable; (1) head/neck, (2) torso or (3) limbs). A relative proportion of skin type V – VI will be included in this sample, as laser treatment for these participants may have limited effect.

This interview explores:

Patient experience of treatment options.Social and psychological lifestyle implications.Expectations, mind-set, confidence, including the perceived views of carers, where appropriate.

Participants are invited to participate in one-to-one interviews as part of the questionnaires presented in the study. The interview selection strategy includes recruiting a broad range of individuals from different genders, ages, clinical sites and severity of the scarring. In addition, the interviews will also elicit Patient Reported Experience Measures (PREM) by capturing the participants’ perceptions of their experience of the process of care.

Interviews are conducted using interview prompt sheets, preagreed with the Patient Advisory Group, to ensure consistency of the interview process. The interview commences with an open-ended introductory question “I am interested in hearing more about your recent experience of … (depending upon which treatment they are provided), please can you tell me about this”. Following this there will be follow-up questions related to:

1)Study and treatment processes.2))Impacts of the treatment process and/or scarring on their daily life.3))Psychological and psychosocial implications of the scarring and/or treatment.4))Work or financial implications of the treatment process and/or scarring.5))Any aspect of their treatment/care that could have been different.6))Whether they would recommend this service to others and why.

Lastly the interview will conclude with another open-ended question:

*“Is there anything else you would like to tell me about the treatment you have received?”*

### Harms reporting procedures

All adverse events should be reported to the CI. Depending on the nature of the event, the reporting procedures below should be followed. Any questions concerning adverse event reporting should be directed to the CI in the first instance. Severity of the adverse event should be reported along with the potential causality. It should also be documented as to whether it represents an unexpected or anticipated event.

## Non serious AEs

All such events, whether expected or not, should be recorded in the participant’s notes.

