#### Secondary objectives

To determine whether there is significant difference between the two groups in:■Observer-rated scar quality at 6 weeks, 12 weeks and 6 months■Patient-rated scar quality at 6 weeks and 12 weeks■Patient-rated QoL at 6 months■Objectively measured scar redness at 6 months■Patient perception of scar change at 6 monthsTo conduct a within-trial economic evaluation of PDL to assess its cost-effectiveness.To qualitatively explore patient experience and psychosocial impact.To assess adverse effect profile of PDL in treatment of burn scars.

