## Serious AEs

An SAE form should be completed and sent to the CI within 24 hours. However, relapse and death and hospitalisations for elective treatment of a pre-existing condition do not need reporting as SAEs. All SAEs should be reported to the REC where, in the opinion of the Chief Investigator, the event was:

‘related’, i.e. resulted from the administration of any of the research procedures; and‘unexpected’, i.e. an event that is not listed above (ELABS Harms) as an expected occurrence

Reports of related and unexpected SAEs should be submitted by the Sponsor within 15 days of the Chief Investigator becoming aware of the event, using the NRES SAE form for non-IMP studies. Local investigators should report any SAEs as required by the National Research Ethics Committee and/or local Research & Development Office. All SAE’s and AE’s will be reported to TSC. AE reports will be sent out to all PIs following each TSC meeting. Receipt of these reports will be signed for in local Trial File.

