### Data management

The data collection tool for this study will be paper CRFs. Data will be entered directly onto the CRFs and considered a source document. The data collection may be conducted by the CRN nurses, the PIs or the HCP involved in the scar assessment. There may be variation between sites, and this will be detailed in the SOPs for each site.

The recruitment sites will store all original signed informed consent forms (model consent form in the *Extended data*
^
71
^). All data will be entered electronically onto a database by the Trial Coordinator at the sponsor site or at the participating site where the data originated. This database (REDCap Cloud) is managed by the CTU. Original study forms will be entered and kept on file at the participating site. Copies of 10% of completed forms will be sent by post to the trial coordinator in batches for checking. The CTU will produce reports on data completeness, flag issues and supervise the Trial Coordinator.

All data is recorded and kept in project file for quality control and will be monitored by the sponsor through the Trial Coordinator. Personal data, as defined by General Data Protection Regulation, is not disclosed without written consent. All personal information is kept for the duration of the study and archiving period, after which it will be destroyed. Data archiving costs are included.

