### Interventions

#### Pulsed Dye Laser (treatment arm)

There are two models of PDL from different manufacturers; Cynergy (Cynosure, West-ford, MA, USA) and the Vbeam (Syneron Candela, USA). The settings to be used are:

10 mm, spot size0.5 ms, pulse duration5 – 9 J cm^-2^, energy fluenceApprox. 10% overlapSingle pass

Laser treatment follows assessment and is performed by a trained laser operator. Where multiple scars are present, the laser operator treats the study scar. Other non-contiguous scars may be treated within the limit of total treated area deemed suitable. The energy is selected to produce a degree of purpura during treatment without the presence of skin blanching. The skin response is instantaneous and should be dark purple to black. Blanching (or whitening) in the treatment area suggests over-treatment and is to be avoided. If the operator is unsure, a pause of up to a couple of minutes can be adopted to verify the skin response. Once the desired response is observed, the operator should treat the entire trial scar.

Skin cooling is administered during the treatment. Almost all patients cope with the pain without any anaesthesia; neither topical nor local. The PPI group agreed that pain, though sensate, is not an issue. If necessary, topical anaesthesia is offered and recorded, if used. This provides comfort for the participant and minimises collateral damage. Post-treatment photographs are taken after treatment. Cool Aloe Vera gel may be offered to the participant to apply to the treated area after treatment and its application will be recorded. This may help to soothe any discomfort and reduce the residual heat. The treated areas do not require dressing and after-care information is provided. The patient is advised to avoid perfumed cosmetics, any abrasive drying, tight-fitting clothes, and any strenuous exercise or swimming in chlorinated water for 72 hours. This will include the use of any pressure garments.

At subsequent visits, the participants are asked to report on any adverse effects of the treatment. The previous settings should be used to start the treatment but the operator may increase the energy in 0.5 Jcm^-2^ steps until a similar response to the previous visit is achieved. All laser settings are recorded for each visit.

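### Adverse effects are asked about only in the laser-arm text, and the one procedure specific to non-serious events is entry in the notes, so harms would be unequally ascertained between arms

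*Protocol article*

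**What the plan says.** The Secondary objectives section includes: "To assess adverse effect profile of PDL in treatment of burn scars". It stands apart from the list of between-group differences.

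The Harms section lists the expected events: blisters, scabbing, excessive oedema, pigmentation change or pain, worsening of the scar, and other. It adds that pigment change often comes from the burn itself.

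On reporting, the article says three things:

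- Harms reporting procedures: "All adverse events should be reported to the CI", with "Severity of the adverse event should be reported along with the potential causality" and "It should also be documented as to whether it represents an unexpected or anticipated event". It then refers the reader to the procedure below that fits the type of event.
- Non serious AEs: "All such events, whether expected or not, should be recorded in the participant’s notes". That is the whole section.
- Serious AEs: a form to the CI within 24 hours. The section also says that AEs as well as SAEs go to the TSC, and that "AE reports will be sent out to all PIs following each TSC meeting".

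On asking participants, the section Pulsed Dye Laser (treatment arm) says: "At subsequent visits, the participants are asked to report on any adverse effects of the treatment". The section Standard care (control arm) has no such sentence.

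On data, the Data management section says: "The data collection tool for this study will be paper CRFs". Adverse events do not appear in the Secondary outcome list or among the assessments in Table 2.

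**The concern.** Two features of the text bear on the safety objective.

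First, the general rule sends the reader to an event-specific procedure, and for non-serious events that procedure names only the participant's notes. The promise that all AEs reach the CI and TSC has no stated step that takes a blister or a patch of scabbing from the notes to those bodies or to the trial data. Serious events have a form and a deadline; non-serious events, which will make up most of the listed harms, have neither in this article.

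Second, participants are prompted in one arm only, as written. Prompted enquiry generally yields more minor events than spontaneous report. Some listed harms also arise without laser, so a count from prompted laser patients set beside unprompted controls mixes a laser effect with a difference in asking. The same imbalance would reach the TSC and the data monitoring committee when they look at events by arm.

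**Working it through.** The plan states no figure on this point, so there is none to reproduce. The check is a comparison of sections, then a bound on the bias.

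**1. Where a non-serious event goes.** Harms reporting procedures: to the CI, with severity, causality and expectedness. Serious AEs: to the TSC, with AE reports to the PIs. Non serious AEs: to the notes. None of these is restricted to one arm, and none excludes the others. They can be read as cumulative, but the section a site would consult for a non-serious event mentions only the notes. The three need to be reconciled.

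**2. Who is asked.** The enquiry sentence is in the laser-arm section, refers to effects of the treatment, and is followed directly by how to set the laser at the next session. Three sessions at six-week intervals from week 0 fall at weeks 0, 6 and 12. Read in that context, the enquiry clearly covers weeks 6 and 12. Whether it covers week 26, the only scheduled visit after the third session, is not stated. For controls nothing is stated at any visit.

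**3. What control data exist anyway.**

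| Listed harm | Measured in both arms |
|---|---|
| Worsening of the scar | Patient and observer POSAS at weeks 0, 6, 12 and 26; 7-point change question at week 26 |
| Pigmentation change | Colorimeter melanin, scar and unburnt skin, weeks 0 and 26; photographs at each assessment |
| Pain | Not as an adverse event; at most through questionnaires |
| Blisters, scabbing, oedema | No scheduled measurement named; photographs only |

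**4. Bound on the bias.** Let p be the true proportion of controls with an event by week 26, q the true proportion in the laser arm, and s_C and s_L the fractions of true events captured in each arm.

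- Observed difference = s_L·q − s_C·p; true difference = q − p.
- Bias = (1 − s_C)·p − (1 − s_L)·q.
- The upward bias is largest when s_L = 1 and s_C = 0, and then equals p.

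The documents give no value for p or for the capture fractions. Assume p = 10%, 30% or 50%, no true laser effect (q = p) and full capture in the laser arm. The spurious excess is then p(1 − s_C):

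| Assumed p | s_C = 0 (bound) | s_C = 0.5 | s_C = 1 |
|---|---|---|---|
| 10% | 10 points | 5 points | 0 |
| 30% | 30 points | 15 points | 0 |
| 50% | 50 points | 25 points | 0 |

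The first column is a limit, not an estimate, because control events remain reportable.

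**5. Precision with equal enquiry.** With 60 per arm analysed (Sample size section) and the same proportion in both arms, the 95% half-width for the difference is 1.96·√(2p(1 − p)/60):

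- p = 0.1: 1.96·√0.0030 = 0.107
- p = 0.3: 1.96·√0.0070 = 0.164
- p = 0.5: 1.96·√0.00833 = 0.179

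So equal enquiry gives an imprecise comparison of about ±11 to ±18 points, but one free of the bias from unequal asking.

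**The case against.** The strongest reply is that the text can be read as sound. Recording in the notes and reporting to the CI and TSC are cumulative steps, the reporting rules apply to both arms, and the choice of CRF page is detail that an article leaves to the full protocol, the CRFs and the SOPs. Table 2 also omits photographs and laser settings, which are certainly recorded. The objective is worded as a profile of PDL, not as a between-group difference, and it can be met descriptively from prompted laser patients, the list in the Harms section and the causality assessments. The primary outcome is untouched.

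Much of this stands, and it rules out three stronger readings that a reader might infer:

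- That non-serious events go nowhere but the notes. The section does not say so, and two neighbouring sections name further recipients.
- That the safety objective cannot be met. A descriptive laser-arm profile is possible.
- That there is no control information. POSAS, the change question and melanin cover worsening and pigment in both arms.

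Nor do the documents say that controls are not asked; they are silent. And the statement under Follow-up duration that scars may deteriorate runs to six months after injury, whereas follow-up ends at seven to nine months after injury, so it supports background worsening for only part of follow-up.

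The reply does not remove the asymmetry. The one enquiry that is written down is placed in the laser arm and tied to the treatment. Scale scores and melanin do not replace adverse-event counts, and they do not cover blisters, scabbing or oedema. A causality judgement made with knowledge of the allocation does not replace a control rate for events that the burn itself can cause.

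**Conclusion.** The point holds as one of unequal ascertainment and unreconciled reporting text. Followed as written, adverse-event counts would be prompted in the laser arm and unprompted in controls, and events that also occur without laser could not be reliably attributed to it. The upward bias in a between-arm comparison of reported events is unknown and lies between nothing and the background rate; the assumed range of 10 to 50 points marks the limit under zero control capture and should not be quoted as an expected size. The conclusion assumes that sites follow the article's wording; a fuller protocol or CRF set may already close part of the gap. It affects a secondary objective only. This is a cheap improvement, not a flaw that undermines the trial.

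**What to change.** 1. In Non serious AEs, add a cross-reference to the CI and TSC reporting rules, and state that non-serious events are captured on the CRF and entered in the trial database as well as in the notes. If a CRF page already exists, naming it is enough.
2. List adverse events as a secondary outcome, matching the stated objective.
3. Use one checklist based on the list in the Harms section, worded about the study scar and not about the treatment, at weeks 6, 12 and 26 in both arms. Add the row to Table 2 and report each item by randomised arm.
4. Have the checklist self-completed, or taken by staff who do not perform the observer POSAS or the colour measurement, and keep the answers from those assessors. A report of blistering or scabbing could reveal the allocation that the Blinding section asks participants not to divulge.

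The cost is a short amendment, at most one CRF page and a few minutes at visits that already take place. Controls will report background events, which is the purpose, and sites must arrange for the answers to bypass the blinded assessors. The article describes recruitment as imminent, so the change is best made before the first week-6 visit: symptoms not asked about at the time cannot be fully recovered later.
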